**3.2 - Sample size calculations.**

To be clinically reliable, the combined selective criteria must satisfy two requirements. First, intracranial injuries requiring neurosurgical intervention must never occur in blunt head trauma victims identified as risk free by the instrument. This is equivalent to requiring a 100% negative predictive value. Second, every blunt trauma victim with a significant intracranial injury must exhibit at least one of the risk criteria. This requirement implies that the sensitivity of decision instrument be 100%.

Verifying negative predictive value and sensitivity at an absolute level is not statistically possible with a finite sample size. However, it is possible to estimate limits for the true values of these proportions using exact statistical relationships. The lower confidence limit of a proportion (such as negative predictive value or sensitivity) is related to the total size of the study population. The quantitative relationship is expressed by the following equation [48]:

[figure not shown]

Where:

P_L_ = Lower confidence limit for the proportion being studied (i.e. the lower confidence limit for the negative predictive value or sensitivity of selective criteria).

X = Number of times the event of interest is observed.

N = Total number of observations.

α = Statistical confidence value (Set to 0.05).

ν_1_ = Degrees of freedom for the numerator; ν_1_ = 2 [ N - X + 1 ]

ν_2_ = Degrees of freedom for the denominator; ν_2_ = 2 X

F_α/2,ν1,ν2_ = One tailed value of the F-distribution with ν_1_ and ν_2_ degrees of freedom.

Validating a given P_L_ to a 95% level of statistical certainty implies that α = 5% (or α = 0.05). The main hypothesis of this study states that selective criteria will detect all intracranial injuries requiring neurosurgical intervention in blunt head trauma victims without missing any such injuries. Thus, for purposes of sample size calculations, for either negative predictive value or sensitivity, the event of interest (presence of one of the risk criteria) should occur with every observation. Hence, X = N.

The degrees of freedom for the numerator and denominator are then given by:

ν_1_ = Degrees of freedom for the numerator; ν_1_ = 2 [ N - X + 1 ] = 2 [ N - N + 1 ] = 2

ν_2_ = Degrees of freedom for the denominator; ν_2_ = 2 X = 2 N

The expression for the lower confidence limit then becomes:

[figure not shown]

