As discussed previously, practical concerns regarding radiographic charges and radiation health effects suggest that selective criteria will still remain cost effective and reduce mortality and morbidity even when missing 10 out of every 1,000 injuries. This implies that negative predictive value need only be verified to a 99.0% lower confidence level, or equivalently, P_L_ = 0.99. Substituting this value in the lower confidence limit equation yields the following algebraic equation for intracranial injury population size N;

[figure not shown]

The numerical solution to this equation is N = 368. Thus, to confirm that the decision instrument has a negative predictive value of at least 99.0%, the study must enroll 368 head injury victims who have none of the risk criteria, and none of whom have intracranial injuries requiring neurosurgical intervention. Since approximately 10% of head trauma victims are free of the risk criteria, this derivation would require a population of 3,680 head trauma victims. Unfortunately, confirming that the instrument has a 99.0% sensitivity requires studying 368 intracranial *injury* victims. Surgically significant intracranial injuries occur in only 1.2% to 1.4% of head trauma cases. Assuming a serious injury prevalence of 1.2% implies that this study will need to prospectively evaluate 31,000 blunt head injury victims. Consequently, study size is driven by the requirements of sensitivity.

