**4. EXPERIMENTAL DESIGN AND METHODS**

**4.1 - Experimental Design**

The study will be conducted as a multicenter prospective evaluation of blunt head trauma patients undergoing computed head tomography. Participating study centers encompass a range of acute care facilities including academic trauma centers, community trauma centers and community emergency departments. Surveying a wide range of hospitals will make the study results generalizeable the majority of mild head injury victims.

The study will use an experimental design similar to that implemented in the previous study *Selective Computed Head Tomography in Blunt Trauma* (PHS Grant No. R01 HS09699). This computed tomographic derivation study is particularly important to the current proposal because it has already evaluated the use of a multicenter network needed to conduct the blunt head injury validation research. In addition, both studies use very similar methodology and protocols. Thus, the core methodology for evaluating blunt head injuries has already been tested in the derivation study. Personnel trained for the earlier study have become experienced with this methodology and can be quickly updated to the new protocols needed for the validation study. Most importantly, the derivation study demonstrates that the methodology for the current proposal is feasible and can be conducted in the clinical environment. The derivation study involved over 800 physicians, as well as a similar number of supporting technicians and nurses, working at 21 institutions, and accumulated over 600 cases per month.

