Because computer generated requests will be required for all emergency department head tomographs, patients who present with non-traumatic indications may be enrolled in the study. Physicians will be required to indicate the non-traumatic nature of these evaluations. To assure compliance with the methods of this proposal, clinicians will still be required to enter relevant study information. This information will be retained in a separate database, and will be analyzed separately from data on blunt head injury victims. This information may be useful in developing selective indications for non-traumatic computed head tomography. However, this information is not relevant to the hypotheses being tested in this study.

Imaging requests may be generated prior to complete data entry in physiologically unstable patients. Clinicians will ultimately complete data entry in these patients, but complete data entry may occur after computed head tomographs have been reviewed. In such cases, the data entry for the case will document the physiologic instability and non-concurrent nature of the data collection. In our previous study, clinicians classified 8.7% of patients as unstable (including 17.5% of patients with intracranial injuries), but were able to complete assessments on all patients. In this regard, the study protocol allowed clinicians to provide expeditious care to even the most severely injured patients, while having a negligible impact on data collection.

Data will be collected on all blunt head injury victims entered into the study. Inclusion will not depend on age, sex, race or ethnic origin. Specific information regarding race will be collected to determine what effect, if any, race may have in evaluating patients for risk of injury. Demographic analyses will be performed on age and sex data. Study sites (Appendix A) have been selected to represent a broad spectrum of medical environments. These sites are expected to enroll a diverse population containing all races and both sexes. All sub-populations will be represented in the study in the same proportions as they present with blunt head injuries.

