It is possible that clinicians may not be able to evaluate individual criteria in some patients. For example, it may not be possible to perform a detailed neurological exam and assess motor strength in an individual who has multiple extremity fractures and is unable to cooperate. Clinicians can indicate such occurrences by designating the presence or absence of the individual criterion as “unknown”. The overall decision instrument will treat these “unknown” responses as abnormal responses. Individual risk criteria will be classified as absent only if they can be tested and found to be absent. Consequently, the decision regarding the ultimate need for tomography is based on measuring individual criteria and determining that they are *all absent* in a given individual. If a patient exhibits any of the criteria, or if one or more of the criteria cannot be assessed, the individual will be labeled positive by the decision instrument. Such patients may harbor a significant intracranial injury and should be considered candidates for tomographic scanning. Clinicians are not to use the “unknown” designation in lieu of an adequate evaluation. Our experience with the cervical spine and head injury derivation studies reveals that study physicians use this designation appropriately.

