Injuries such as isolated linear or basilar skull fractures, solitary small cerebral contusions, localized subarachnoid hemorrhage less than 1 mm thick, thin subdural hematomas less than 4mm thick, isolated pneumocephaly, and closed depressed skull fractures that do not violate the inner table will not be considered to be significant injuries [63]. Coincidental or congenital abnormalities will also not be considered to be significant intracranial injuries. Chronic subdural hematomas, without evidence of acute change, will be considered to be coincidental injuries and will not be considered to be significant acute injuries. Chronic subdural hematomas that exhibit any recent change, or those that are of indeterminate age, will be considered to be acute significant injuries.

Research assistants, blind to classification by the decision rule, will review the medical records of patients with positive tomographic scans to determine whether or not the patient received neurosurgical intervention. The need for neurosurgical intervention is defined as any of the following within seven days of the initial injury [63]:

1 – Death due to intracranial injury.

2 – Intubation for management or support of head injury.

3 – Craniotomy, elevation of skull fracture or intracranial pressure monitoring.

Cases involving death or intubation will be reviewed by the physician liaison to determine, on the basis of their best clinical judgment, whether there was a causal relationship between the event and the patients intracranial injury. The liaisons will be instructed to consider these events as causally related to intracranial injury unless there is compelling evidence to the contrary. Patients will not be considered to have received neurosurgical intervention if their death is clearly due to causes unrelated to their head injury, or if they were intubated solely to expedite care.

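### Severe cases that the instrument cannot miss count in the pooled primary sensitivity and toward the 368, and no rule says how the mild-injury claim is to be supported

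*Protocol*

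**What the plan says.** **Entry.** Sections 4.2 and 4.3.2.1 take every blunt head trauma patient who has head CT. There is no GCS, coma or intubation exclusion.

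**Instrument.** Appendix C counts a GCS of 14 or less as abnormal alertness, which is one of the criteria. Section 4.3.3 adds that "if one or more of the criteria cannot be assessed, the individual will be labeled positive by the decision instrument".

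**Outcome.** Section 4.3.5.1.2 reviews the records of patients with a positive CT. Neurosurgical need is met within seven days of injury by death from the injury, by "Intubation for management or support of head injury", or by listed procedures. Death and intubation are attributed to the injury unless the evidence against is compelling. Intubation done only to speed up care does not count.

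**Analysis and stop.** Section 4.3.7 makes one pooled sensitivity the primary outcome. Section 4.3.10.3 continues to 368 outcome cases, or stops at 10 missed ones.

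**Population generalised to.** Section 4.1 states: "Surveying a wide range of hospitals will make the study results generalizeable the majority of mild head injury victims". Section 4.3.7.1.2 also describes the population as minor injury.

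**Severe patients.** Section 4.3.9.1 says the critically ill will in general fall outside mild status. Section 4.3.8.3 keeps unstable patients' data in a separate database. Section 4.3.7.1.2 removes only incomplete records. Of the derivation study, section 4.3.2.1 reports that "clinicians classified 8.7% of patients as unstable (including 17.5% of patients with intracranial injuries".

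**The concern.** A patient who is comatose or intubated when assessed is instrument-positive whatever the merit of the eight criteria taken together. If that patient also has a positive CT and a qualifying outcome, the case enters both numerator and denominator of sensitivity as a success that could not have been a failure. Nothing requires the intubation to come after the assessment.

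The use proposed for the instrument is to omit CT in patients who show none of the criteria. Evidence on sensitivity near that boundary comes from outcome cases who could have been labelled low risk. The more of the 368 that could not, the less the 99.0% limit says about mild injury. The 10-miss stop loses force in the same way.

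The protocol does not settle the matter. Section 4.3.9.1 discounts bias from late-completed forms by saying that critically ill patients are in general outside mild status, but no eligibility or analysis rule puts them there. Section 4.3.8.3 separates the unstable patients' data without saying whether complete records count in the primary sensitivity. Read alone, section 4.3.7.1.2 implies that they do.

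**Working it through.** **Inputs.** All are from section 3.2 unless stated.
- α: "α = Statistical confidence value (Set to 0.05"), with the F quantile taken at α/2, so 0.025 in the lower tail.
- Target limit 0.99: "negative predictive value need only be verified to a 99.0% lower confidence level", then applied to sensitivity as well.
- No misses: "the event of interest (presence of one of the risk criteria) should occur with every observation", so X = N.
- Prevalence of neurosurgical cases: 1.2% for planning.
- f, the share of the 368 outcome cases that are positive by construction: **not in the protocol**, so treated as an assumption over a range.

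**Reproducing the plan's figure.** With X = N the exact lower limit is P_L = 0.025^(1/N). Setting P_L = 0.99 gives N = ln(0.025)/ln(0.99) = 367.04, rounded up to 368. This agrees with the plan: "The numerical solution to this equation is N = 368". Enrolment is 368/0.012 = 30,667, which matches the stated 31,000. The arithmetic is correct.

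**Cases left to test the instrument.** With m = 368 × (1 − f), rounded, and no misses, P_L = 0.025^(1/m):

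| f (assumed) | m | Exact 95% lower limit |
|---|---|---|
| 0 | 368 | 99.0% |
| 10% | 331 | 98.9% |
| 17.5% | 304 | 98.8% |
| 25% | 276 | 98.7% |
| 50% | 184 | 98.0% |
| 75% | 92 | 96.1% |

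The 17.5% row borrows the unstable share among derivation patients with intracranial injury. It is only a proxy: unstable is not the same as comatose, and those patients were not all neurosurgical cases.

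**Effect on the pooled estimate and the stop.** Suppose, as an illustration, that true sensitivity is 98% in the testable cases. At f = 50% the pooled value is 0.5 + 0.5 × 0.98 = 99.0%. The chance of no misses is 0.98^368 = 0.06% at f = 0 and 0.98^184 = 2.4% at f = 50%. The binomial chance of 10 or more misses falls from 20.6% (368 cases) to 0.4% (184 cases).

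**How large f could be.** Derivation figures: 0.175 × 917 = 160 unstable patients with injury. A prevalence of 1.2% to 1.4% of 13,728 is 165 to 192 neurosurgical cases. If every unstable injured patient met the outcome, f would be 160.5/192.2 = 83.5% to 160.5/164.7 = 97.4%. Section 2, however, reports 14 neurosurgical cases with none of the Canadian high-risk factors, hence no persistently abnormal GCS. With 165 cases that caps f at about (165 − 14)/165 = 91.5%. Below that cap, the protocol's figures do not locate f.

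**The case against.** **The aim is broader than mild injury.** The title, aims, hypotheses and primary outcome concern blunt head injury generally, and mild or minor appears only in side remarks. The sentence in section 4.1 is mainly about hospital mix. This stands: all-severity sensitivity is a valid estimand. It does not remove the mismatch with the generalisation in section 4.1 or with the argument in section 4.3.9.1.

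**A restricted analysis exists.** A reader might infer that no mild-injury analysis is planned. That is not so. Section 4.3.7 will report the NEXUS instrument among patients meeting the Canadian rule's entry criteria, which by section 2 exclude GCS below 13 and unstable vital signs. But it is secondary, and narrower than mild injury: it also drops focal deficit, coagulopathy, seizure, patients under 16 and those without loss of consciousness, amnesia or disorientation.

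**Not every severe patient is automatic.** This stands. A comatose patient without a positive CT is a false positive, causation is adjudicated, and intubation only to speed up care is excluded.

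**NPV is untouched.** Severe patients are instrument-positive, so they enter neither true nor false negatives. At 10% to 12.9% low risk, 31,000 patients yield about 3,100 to 4,000 low-risk patients, and with no misses the exact lower limit is about 99.9%. That is real evidence on the patients whose scans would be omitted. It cannot replace sensitivity, since at 1.2% to 1.4% prevalence an instrument unrelated to injury would already have an NPV of 98.6% to 98.8%.

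**A subgroup table could sit in an SAP.** True of the table, but not of the conflict between sections of the protocol.

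**Conclusion.** The point holds in a limited form. The 368 is right for the pooled, all-severity population, but its 99.0% lower limit does not carry over to mild injury. The protocol also leaves unsettled whether complete unstable records are in the primary sensitivity. Assuming no misses, the limit in the testable cases is 98.8% if 17.5% of cases are automatic, 98.0% at 50% and 96.1% at 75%. The loss is small at the low end and material at the high end.

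A reader might infer that automatic cases make up nearly all of the 368. The protocol does not support this: the figure requires every unstable injured patient to have met the outcome, unstable is not comatose, and the 14 cases in section 2 rule out the 97% end. A reader might also infer that the pooled sensitivity is invalid, or that performance in alert patients goes essentially untested. Neither follows, given the breadth of the aims, the Canadian-rule analysis and the NPV.

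**What to change.** Keep enrolment and the 368-case stop as they are.

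1. Reconcile sections 4.1, 4.3.7.1.2, 4.3.8.3 and 4.3.9.1, stating whether complete records of unstable patients count in the primary sensitivity.
2. Label the pooled sensitivity as all-severity.
3. In section 4.3.7, pre-specify sensitivity, NPV and specificity, with case counts and exact intervals, in stable patients with GCS 13–15. Within them, do the same in alert patients (eyes open, oriented and obeying commands all answered Yes).
4. Rest any conclusion about mild injury on that restricted estimate and its own lower limit.
5. Ideally, add one form item: intubated before assessment, yes or no.

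Stability and the three alertness items are on the Appendix B form, and section 4.3.3 says the GCS score is assessed. Because the sample form shows only the three items, confirm that the score itself is recorded.

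The cost is one table, possibly one or two form items, and a lower limit below 99.0% for the restricted group. Removing pre-intubated cases from the 368 is not recommended as a cheap alternative. Keeping 368 informative cases would take 368/(1 − f) outcome cases: 447 at f = 17.5% (about 37,200 enrolled at 1.2%) or 736 at 50% (about 61,300).

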**4.3.5.2 - Radiographic Request Generation**

Radiographic request forms will be handled by dedicated computer systems. These devices will submit requests for computed head tomographic imaging each time a complete data record is entered. This will aid in protecting the integrity of the data and prevent accidental data entry or tampering.

**4.3.6 - Database Management**

A database application will be used to display the data questionnaire, provide input fields for survey responses, and direct storage and management of study data. This system will employ a redundant entry system that requires each response to be recorded twice. Discrepancies between responses will generate a prompt that will require the data to be re-entered until concordant responses are recorded. This process will help minimize the potential for data corruption from keyboard entry errors. Our database applications have been previously developed, tested and implemented in the prior studies on selective criteria in cervical spine injury and selective tomographic imaging in blunt head trauma. Captured data will be initially stored in a database file on the microcomputer hard disk drive until the next weekly data transfers and concatenation. In addition to data transfers, data will remain in each system, to serve as an ultimate backup, until completion of the entire study. Once a complete survey form has been entered into the database it will be unalterable by the affiliated site hospital. Error correction will follow the protocols described below. The examining clinicians will have access only to survey entry forms, while site liaisons and coordinators, and UCLA data analysts will be able to examine and transmit entire data sets.

A multi-functional database management application and programming language will be used as the main database management tool to create, store, maintain and analyze data records. This application will be used to program file maintenance utilities (i.e. concatenating programs, search routines, error detection programs, etc.), and its analytic capabilities will be used extensively in data analyses.

**4.3.7 - Data Analysis**

The primary outcome for the study is the point measure and associated 95% confidence interval for the sensitivity of the decision instrument in identifying patients who require neurosurgical intervention. Additional operator characteristics of interest for this population include the negative predictive value and specificity. Secondary outcomes include the sensitivity, negative predictive value and specificity of the instrument in detecting patients who harbor clinically significant intracranial injuries as described by the criteria defining positive CT imaging (see 4.3.5.1.2 - Injury Diagnosis above). A further secondary goal of the study is to determine and compare the operator characteristics of both the NEXUS head CT instrument, as well as both forms (“high risk” and “medium risk”) of the Canadian head CT instrument, among patients who meet the inclusion and exclusion characteristics for classification by the Canadian rules.

